### Calculation of sample size and statistical analyses

Sample size will be estimated by NQuery Advisor v4.0 (Statistical Solutions, Boston, MA, USA). For this trial, it has been determined prospectively that α = 0.05 and 1-β = 0.90, and that the standard deviation will be 1.81 according to the three group subsets. According to a previous study [20], we anticipated that a mean frequency of migraine attacks in the non-acupoint group is 3.7 whereas, in the individualized acupoint group, it is 2.7. Hence, a minimum difference of clinical effect is 1.0. Thus, ≥ 70 participants are required for each group. To compensate for a prevalence of withdrawal of 15%, we plan to enroll 249 participants in the three groups, with 83 patients for each group.

For the final outcome analysis, we will make all pair-wise comparisons using a general linear model adjusted for baseline value, age, sex, clinical center, and disease course. The comparison between the individualized acupoint group and non-acupoint group is the primary interest in this study. In general, the summarization of difference is in accordance with CONSORT expectations, which will be addressed using effect size estimates and the associated confidence intervals.

All data in this trial will be assessed by Brightech-Magnasoft CIMS, with SPSS v13.0 (SPSS, Chicago, IL, USA) and SAS v9.1.3 (SAS, Cary, NC, USA). All analyses will be done on the intention-to-treat (ITT) population (that is, any participant randomized regardless of whether he/she receives any treatment). Missing data will be replaced according to the principle of multiple imputation. In addition, the per protocol (PP) population will be analyzed. The results of ITT and PP analyses will be compared to ascertain if the results are consistent. Moreover, analysis of variance (ANOVA) for repeated measures will be used for numerical variables. The Chi-square test will be used for categorical variables. *P* < 0.05 will be considered significant.

## Discussion

Pragmatic and explanatory randomized controlled trials play a significant part in the evaluation of healthcare interventions in China and overseas [29]. Explanatory trials are designed to ascertain whether a treatment has efficacy under ideal experimental conditions. Pragmatic trials are used to discover how effective a treatment is in routine everyday practice, with the aim of providing evidence that will help policymakers, practitioners or patients make choices between two interventions [30]. Pragmatic trials are used to ascertain if a treatment is beneficial under conditions close to those that operate in routine care, whereas effectiveness studies adopt a more pragmatic approach [31,32]. The greatest strength of pragmatic trials is that they can deliver evidence of effectiveness in the causal effects of a treatment [33].

The results of several trials suggest that an enhanced placebo effect impacts the acupuncture effect, which may explain patients’ positive beliefs and expectations of benefit of acupuncture and a benign acupuncturist-patient relationship [18,34-38]. We believe that this trial will demonstrate that the acupuncture effect is not due primarily to the physiological effects of acupoints. These influential factors have been standardized as strictly as possible and the selection of non-acupoints is different from those in previous studies. However, we cannot rule out the possibility that intervention using non-acupoint acupuncture may have some physiological effects. We designed a waiting-list group to ascertain if a psychological effect exists. There is no therapeutic intervention in the waiting-list group. Hence, we anticipate that the placebo effect from the acupuncturist-patient relationship and patients’ expectancy of benefit of acupuncture may be zero compared with the non-acupoint group. Furthermore, using parameters to attest to the specificity of acupoints, we will use non-acupoint stimulation in the control group. All participants will be followed-up.

The strength of our trial is strict central randomization, which will ensure adequate concealment of allocation and an equal chance of assignment in each group at all centers. Successful data collection from headache diaries and flexibility in treatment prescription will improve the compliance of practitioners. However, our trial will be limited by our inability to prevent patients knowing whether they are receiving treatment or waiting-list treatment. This factor may cause a high dropout rate in the waiting-list group because patients expect to receive acupuncture treatment when they join the trial. To prevent the expected high dropout rate, patients in the waiting-list group will receive 20 sessions of free acupuncture treatment after the entire course.

Briefly, the purpose of this trial is not to evaluate the efficacy of acupuncture as a painkiller, but to evaluate the duration and intensity of the effectiveness of acupuncture for the prophylaxis of MWoA in daily clinical practice in China.

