#### *Individualized acupoint group*

In the individualized acupoint group, the acupoint prescriptions used will be personalized to each participant and at the discretion of the acupuncturist. Differentiating the location of meridians is an important part of TCM theory, so it was used to select acupoints on the basis of the evolution of the patient’s symptoms. *Fengchi* (GB20) and *Shuaigu* (GB8), having the highest frequency, were selected as obligatory acupoints. Additional points, which were used in a previous study [25], could be chosen according to syndrome differentiation of meridians: (i) *Shaoyang* headache (headache only attacks the temporal side): *Waiguan* (SJ5) and *Yanglingquan* (GB34); (ii) *Taiyang* headache (headache involves the occiput): *Kunlun* (BL 60) and *Houxi* (SI3); (iii) *Yangming* headache (headache involves the forehead): *Hegu* (LI4) and *Neiting* (ST44); (iv) *Jueyin* headache (headache involves the vertex): *Taichong* (LR3) and *Qiuxu* (GB40).

The acupuncturist responsible for the treatment will insert sterile, single-use filiform acupuncture needles (length, 25 to 40 mm; diameter, 0.25 mm) and auxiliary acupuncture needles (without manipulating the needles) of length 13 mm and diameter 0.18 mm after first disinfecting the skin with the participant lying down. The needles used are Hwato needles (Suzhou, China). The puncture will be made according to TCM standards to a depth of 0.3 to 1 cm depending on the points selected. Insertion will be followed by the stimulation methods of lifting and thrusting combined with twirling and rotating the needles to produce a sensation known as *Deqi*. Acupoints on the left and right side are employed alternatively, and punctured by filiform needles unilaterally. Auxiliary needles will be punctured 2 mm lateral to each acupoint to a depth of 2 mm without manual stimulation. This method has been used successfully in our previous study [20,26]. Han’s acupoint nerve stimulator (HANS; model LH 200A; TENS, Nanjing, China) will be connected after needle insertion.

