#### *Non-acupoint control acupuncture*

Participants assigned randomly to this group will be given non-acupoint acupuncture, i.e., insertion of acupuncture needles at four bilateral non-points. The protocol of non-acupoints was developed in our latest acupuncture clinical trial [27]. The method will not differ from that used for the individualized acupoint group except for that an attempt will not be made to yield the *Deqi* sensation.

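### The acupoint versus non-acupoint contrast cannot attest to acupoint specificity, because the arms also differ in Deqi manipulation and in individualized versus fixed site selection

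*Protocol article*

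**What the plan says.** All references are to the protocol article.

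- **Purpose of the control (Discussion):** "using parameters to attest to the specificity of acupoints, we will use non-acupoint stimulation in the control group".
- **Primary contrast (Calculation of sample size and statistical analyses):** "The comparison between the individualized acupoint group and non-acupoint group is the primary interest in this study".
- **Acupoint arm (Individualized acupoint group):** the prescription is "personalized to each participant and at the discretion of the acupuncturist", within two obligatory points plus pairs chosen by headache location. On technique: "Insertion will be followed by the stimulation methods of lifting and thrusting combined with twirling and rotating the needles", with the aim of producing Deqi. On side: "Acupoints on the left and right side are employed alternatively, and punctured by filiform needles unilaterally".
- **Control arm (Non-acupoint control acupuncture):** the treatment is "insertion of acupuncture needles at four bilateral non-points", and the method is said to be the same as in the acupoint arm "except for that an attempt will not be made to yield" Deqi. The Interventions section and Table 1 list the same four sites for every participant.
- **Caveat (Discussion):** needling at non-points may itself have some physiological effect. The Discussion gives no other caveat about interpreting this contrast.

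**The concern.** To show that acupoints are specific, the two needled arms would have to be alike in everything except whether the needles are at acupoints. Here they are not. If the trial finds fewer attacks in the acupoint arm, the cause could be the manipulation, the tailoring, the location of the points, or a mixture. A report that follows the Discussion would read such a result as evidence for acupoint specificity, which the design cannot supply. The single caveat does not warn of this. An active control would make the difference between arms smaller, whereas Deqi and tailoring affect what a difference means.

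**Working it through.** **1. The plan's own figures.** The inputs, from the sample size section, are a difference of 3.7 − 2.7 = 1.0 attacks, SD 1.81, α = 0.05 (taken as two-sided; the text does not say) and power 0.90.

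- Normal approximation: n = 2 × (1.960 + 1.282)² × 1.81² / 1.0² = 2 × 10.51 × 3.276 ≈ 68.9, so 69 per group.
- Two-sample t-test: 69.8, so 70 per group, as stated.
- Withdrawal: 70 / (1 − 0.15) = 82.4, so 83 per group, and 3 × 83 = 249, as stated.

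The sample size reproduces. The 1.0 it is built on is the anticipated difference between the two arms as delivered. It is not a difference for point location.

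**2. The two needled arms side by side.**

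| Feature | Acupoint arm | Non-acupoint arm | Separable from location? |
|---|---|---|---|
| Needle location | Acupoints | Four non-points | This is the feature of interest |
| Manipulation for Deqi | Yes | Not attempted | Yes in principle, but not in this design |
| Choice of sites | Individualized | Fixed | Partly: much of it is a choice among acupoints |
| Body region | Two obligatory points, GB20 and GB8, plus chosen pairs | Arm, forearm and lower leg | No: it is part of location |
| Side needled | Unilateral, alternating | Described as bilateral | Unclear from the text |

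**3. What the contrast identifies.** Write the difference in mean attack frequency between the two arms as

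Δ = L + D + T,

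where L is the contribution of point location, D that of Deqi manipulation and T that of individualized selection (any interaction can be absorbed into these terms). The two arms give one equation in three unknowns. For example, L = 1.0 with D + T = 0, and L = 0 with D + T = 1.0, both give Δ = 1.0 and the same expected data.

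The waiting-list arm does not help. It adds the contrast of non-point needling with no treatment, in which acupoint location, Deqi manipulation and individualized selection are all absent from both sides. Covariate adjustment does not help either. The model adjusts for baseline value, age, sex, center and disease course, and D and T do not vary within an arm by design.

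**4. Illustration of size.** This assumes a hypothetical comparison that did isolate location, with 70 per group and the same SD. Power would be 90% if location carried the full 1.0 attack, 69% for 0.75, 37% for 0.5 and 13% for 0.25. The shares are assumptions; the document gives none. In the trial as designed the share cannot be estimated at any sample size.

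**The case against.** The strongest case on the other side has four parts.

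- **The claim is marginal.** The specificity phrase is one sentence in the Discussion. The stated aims concern effectiveness, safety, comparison with placebo, and the duration and intensity of effect in daily practice. For those aims, comparing a package with a sham is legitimate. That stands, and it is why the criticism stops at the inference. Still, the sentence is the stated reason for choosing this control, and this control forms the contrast of primary interest.
- **Deqi is disclosed.** The control section says openly that "an attempt will not be made to yield the" Deqi sensation, and it presents the control as developed in an earlier trial by the same group. Disclosure makes this a deliberate choice, but it does not make the specificity reading valid.
- **The protocol does not commit to a positive specificity finding.** The same paragraph expects the effect not to be due mainly to the physiology of acupoints. That is also a statement about points, and the same contrast cannot settle it alone.
- **The differences can be over-counted.** A reader might infer four separate confounders: Deqi, tailoring, body region and side. The text does not support that count. Body region is an aspect of where needles are placed, so it belongs to the location difference. Tailoring is mostly a constrained choice among acupoints, although individualized versus fixed selection remains a real difference. On side, a reader might see a flat contradiction between the two intervention sections. But the control section says the method is otherwise the same, and the site list names no side, so bilateral may describe points that exist on both sides and are used alternately.

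**Conclusion.** The point holds in a limited form. The primary contrast estimates the effect of individualized, Deqi-seeking acupuncture as a package against fixed non-point needling without Deqi. It cannot attest to acupoint specificity, because Deqi manipulation, and to a lesser degree individualized selection, coincide with arm for all 166 participants in the needled groups. Deqi alone is enough for this conclusion; it does not depend on body region or side.

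A reader might go further and infer that the primary comparison is biased or the trial underpowered. The document does not support that: randomization protects the package comparison, and 70, 83 and 249 all reproduce. No figure in the plan changes. What changes is the conclusion that a positive result would allow.

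The verdict assumes that the arms are delivered as described and that the full protocol has no further needled arm matched on Deqi. The article describes three arms only.

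**What to change.** 1. In the Discussion, and wherever the rationale is carried into the analysis plan or the report, remove the statement that the control will attest to acupoint specificity. Suggested replacement: *The comparison of the individualized acupoint and non-acupoint groups estimates the effect of individualized acupuncture with manipulation to obtain Deqi, as a whole, relative to needling at fixed non-points without Deqi. The groups differ in manipulation and in site selection as well as in point location, so a difference will not be attributed to acupoint location alone.*
2. Set this beside the existing caveat about physiological effects of non-point needling, so that both limits on interpretation appear together.
3. Separately, reconcile the Individualized acupoint group and Non-acupoint control acupuncture sections on unilateral and bilateral needling, so that the statement that only Deqi differs agrees with the descriptions of each arm. Which description is correct is for the investigators to say.

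The cost is a change of wording and a narrower mechanistic claim. Treatment, sample size and analysis stay as they are. The Trial status section reports that recruitment is under way, so the change can be made before any result is interpreted.

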## Trial status

This study is currently recruiting patients. This procedure started on 15 October 2012. This trial is anticipated to be completed on 15 September 2014.

## Abbreviations

MWoA: Migraine without aura; NSAIDs: Non-steroidal anti-inflammatory drugs; TCM: Traditional Chinese medicine; RCTs: Randomized controlled trials; IHS: The International Headache Society; CIMS: Clinical Information Management System; SMS: Short message service; CONSORT: The Consolidated Standards of Reporting Trials statement; VAS: Visual analog scale; AE: Adverse event; SAE: Serious adverse event; MSQ: Migraine-Specific Quality-of-Life Questionnaire; SAS: Zung self-Rating anxiety scale; SDS: Zung self-rating depression scale; ITT: Intention-to-treat; PP: Per protocol; ANOVA: Analysis of variance.
